## Abstract

**Background:**

Various interventions have been tested to achieve adherence to anti-psychotic maintenance medication in non-adherent patients with psychotic disorders, and there is no consistent evidence for the effectiveness of any established intervention. The effectiveness of financial incentives in improving adherence to a range of treatments has been demonstrated; no randomised controlled trial however has tested the use of financial incentives to achieve medication adherence for patients with psychotic disorders living in the community.

**Methods/Design:**

In a cluster randomised controlled trial, 34 mental health teams caring for difficult to engage patients in the community will be randomly allocated to either the intervention group, where patients will be offered a financial incentive for each anti-psychotic depot medication they receive over a 12 month period, or the control group, where all patients will receive treatment as usual. We will recruit 136 patients with psychotic disorders who use these services and who have problems adhering to antipsychotic depot medication, although all conventional methods to achieve adherence have been tried. The primary outcome will be adherence levels, and secondary outcomes are global clinical improvement, number of voluntary and involuntary hospital admissions, number of attempted and completed suicides, incidents of physical violence, number of police arrests, number of days spent in work/training/education, subjective quality of life and satisfaction with medication. We will also establish the cost effectiveness of offering financial incentives.

**Discussion:**

The study aims to provide new evidence on the effectiveness and cost effectiveness of offering financial incentives to patients with psychotic disorders to adhere to antipsychotic maintenance medication. If financial incentives improve adherence and lead to better health and social outcomes, they may be recommended as one option to improve the treatment of non-adherent patients with psychotic disorders.

**Trial Registration:**

Current controlled trials ISRCTN77769281.

## Background

Various clinical interventions have been tested to achieve adherence in non-adherent patients with psychotic disorders, including compliance therapy, psychotherapy, family education, telephone prompting and psycho education. A review focusing on studies involving patients with chronic health problems [1] and a meta-analysis of studies to enhance adherence in psychiatric patients [2] found a modest effect of some interventions (effect size of .36 in psychiatric patients). Yet, there is no consistent evidence for any intervention to significantly improve medication adherence in non-adherent community patients with psychotic disorders.

Guiffrida and Togerson, 1997 [3] conducted a systematic review on financial incentives to increase adherence to health care treatments. They identified 11 randomised controlled trials, all from the USA. In 10 studies financial incentives enhanced adherence to anti-tuberculosis drugs, dental care, a weight reduction programme, substance dependency treatment, and anti hypertensive medication with odds ratios of up to 7 for anti-tuberculosis treatment. Only one study in the review addressed a mental health issue, i.e. adherence to cocaine dependency treatment. One non-randomised study of patients with dual diagnosis found that modest rewards enhanced attendance to the programme [4].

Since there is no published review specifically on studies in patients with mental health problems, we conducted our own review. The following databases were searched for studies: AMED, EBM, EMBASE, MEDLINE and PsycINFO. The following keywords were combined simultaneously to identify studies: medication, therapy, appointment, compliance, adherence, mental health, mental illness and psychiatr, with the terms incentive, compliance, money, payment, contingency management, voucher and material. We found 13 USA based studies [4-16] where incentives have been used to encourage adherence to treatment in people with mental health problems, 10 of which included people with substance misuse and mental health problems. One study was carried out in the UK [17]. Treatment included attendance of therapeutic sessions and out-patient clinics, and abstinence from smoking or substance abuse. Incentives offered were in the form of a direct payment of vouchers, money or tokens. Nine out of the fourteen studies were within-subjects designs and four studies were controlled trials. Two controlled trials examined the effect of offering incentives to promote abstinence from substances, one studied active involvement in inpatient group meetings and one combined attendance at compensated work therapy and abstinence from substances. In all of the studies, the individuals' adherence/abstinence was significantly improved when incentives were offered. In half of the studies, the improvement in outcome was maintained even when the incentive had been taken away. None of these studies referred to any problems or concerns raised in offering incentives. Yet, we did not find a single controlled study testing financial incentives to improve medication adherence in patients with mental health disorders.

A recent publication from the UK reported the use of financial incentives in non-adherent patients in Assertive Outreach Teams (AOTs) [17]. Four out of 5 patients who were offered the scheme accepted. All had improved adherence to medication and three remained without hospital admissions throughout the observation period although they had been frequently admitted before the scheme. No wider research has so far been published.

The use of financial incentives to increase adherence to anti-psychotic medication also raises ethical concerns as shown in a survey of AOT managers in England [18]. A recent study (Priebe et al, in preparation) explored the views and attitudes of different stakeholder groups related to the use of financial incentives in mental health care. Practically all stakeholder groups identified the issue of effectiveness as critical for their view of the intervention and asked for systematic research to establish its effectiveness.

A clinical trial on the effectiveness of financial incentives will inform the ethical debate on the principle of providing such an intervention [18]. One of four categories for judging the ethical dimension of medical interventions is their beneficence [19]. Beneficence is closely linked to effectiveness, and identifying effectiveness requires a randomised controlled trial. Although there may be various indications that financial incentives are likely to increase adherence to anti-psychotic maintenance medication in previously non-adherent patients, the effectiveness and cost-effectiveness of the intervention has never been established in a randomised design, and a randomised controlled trial is required before the wider use of the intervention should be recommended.

## Methods

### Design

In a cluster randomised controlled trial, community teams caring for patients with psychotic disorders in the community, currently AOTs, will be randomly allocated to the intervention group or control condition. The allocation of teams, and not individual patients, will prevent contamination of practice within teams and facilitate the assessment of overall experiences in teams with the practice. It will also make it possible for teams in the experimental group to offer financial incentives to further patients outside the study, without compromising the study design. Teams might consider this to avoid a sense of unfairness among patients cared for by the same team or simply to have more patients benefiting from the intervention. Outcomes will be analysed on the level of individual patients. The effect of clustering of patients within teams will be controlled for in a mixed effects model. The trial will not be 'blind', as masking of patients and clinicians is impossible. Yet, the primary outcome criterion (percentage of injections taken) and secondary outcomes, with the exceptions of global clinical improvement which is rated by clinicians and subjective quality of life and treatment satisfaction which is rated by patients, can be obtained objectively and are taken from the medical records, and should therefore not be influenced by lack of masking.

AOTs will first be approached and informed about the study through the National Forum for Assertive Outreach and local collaborators at study centres in London, Oxford and Liverpool. We will approach around 100 AOTs that are based within reasonable distance of the study sites so that regular travelling to the teams is realistic. AOTs will receive information about the study on regional and national meetings of AOTs and material circulated through email. This will be followed up by direct telephone calls of the director of the National Forum for Assertive Outreach and other members of the research team including the research assistants. Although we expect that a number of teams will object to either the practice of offering financial incentives or being randomly allocated within a research design or both, informal consultations showed that we can expect more than 36 teams to volunteer for participation in the study. To include an AOT in the pool of eligible teams we will ask for preliminary informed consent by the team manager. AOTs already practising a financial incentive scheme will be excluded. Yet, a survey conducted in 2006 [18] identified only one AOT in England using financial incentives at the time, and this number is unlikely to have increased substantially since. We will then randomly select 36 teams out of the pool of volunteering teams, allowing for two teams to drop out in the further procedure before the trial begins.

All recruited teams will be visited by a member of the research team to explain the nature of the intervention and the study. Clinicians and managers in all teams will receive a structured presentation addressing the research background, the design of the trial, and ethical as well as practical issues of implementation. Written informed consent to participate will then be obtained from team managers and psychiatrist consultants.

The next step will be to identify patients in each team fulfilling the inclusion criteria. We expect the number of patients in most teams to vary between 5 and 8. We expect to recruit 4 patients per team and will randomly select patients if required. These patients will be informed about the study by a clinician and then approached by a researcher for written informed consent for their data to be used in research and for participating in a trial, in which patients in some but not all teams are offered financial incentives to improve medication adherence. If patients cannot be contacted initially or do not provide written informed consent, further patients fulfilling the inclusion criteria will be recruited from the participating teams until the total sample size is reached. Selecting and recruiting patients before randomisation is essential to avoid a possible bias in the selection and recruitment procedures based on awareness of whether patients will be in the experimental or control group. After this one-off contact between the patient and a research assistant, there will be no requirement for further contacts between research assistants and patients in either group. Following the initial interview, patients are not required to participate in any research interviews or assessments at any point of time. This simple and non-intrusive procedure is meant to minimise the number of non-consenting patients (which always is a problem with research in challenging patients in AOTs) and avoid a selection bias as far as possible. Only if patients volunteer to be contacted at the end of the trial again, a researcher will attempt such contact (possibly via telephone) to ask 11 questions on patient reported outcomes.

After the recruitment of patients, 34 AOTs will be randomly allocated to the intervention or control condition stratifying for the type of catchment area (i.e. inner city, suburban or rural).

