### Outcome measures

The primary outcome is adherence to anti-psychotic maintenance medication during the 12 month trial period. Adherence will be measured, objectively, as the percentage of prescribed depot injections actually taken. As the primary outcome, the percentage will be used as a continuous variable. However, we will also analyse the percentage in a dichotomised way, comparing the ratio of patients with 'good' adherence (i.e. =80% of prescribed depots taken [20]) in the two conditions.

Further secondary outcomes are:

a) The time 'slippage' of taking depots, defined as the percentage of the prescribed time interval that has expired before the depot is taken;

b) Clinical improvement as assessed on the Clinical Global Impression Scale (CGI) [21] by the treating consultant psychiatrist at the end of the 12 month period;

b) Number of involuntary and voluntary hospital admissions during the trial period;

c) Costs of care: data on the use and frequency of use of inpatient care, outpatient care (including home visits, home treatment), and other health services during the 12 month treatment period will be obtained from case notes and electronic administrative data bases. Costs for the intervention will be estimated for each participating team from information provided by staff. Established national unit costs will be used to estimate direct health care.

d) The number of attempted and completed suicides, incidences of physical violence, police arrests and days spent at work/training/education will also be recorded over the 12 month trial period.

e) Subjective quality of life and satisfaction with medication which will be assessed at the beginning and end of the intervention period using the 11 item scale established in the DIALOG trial [22]. The scale contains 11 items asking patients to rate their satisfaction with 8 life domains and 3 treatment aspects, one of which is medication, on a scale ranging from 1 (lowest satisfaction) to 7 (highest satisfaction).

f) Continuation with financial incentives (in intervention group only) and adherence during a 6 month follow up period will be taken from the medical records.

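### The Design section wrongly treats suicide attempts, violence, arrests and work days as protected from the lack of masking because they come from the records

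*Protocol article*

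**What the plan says.** The Design section concedes the open design: "The trial will not be 'blind', as masking of patients and clinicians is impossible". It then says that the percentage of injections taken and the secondary outcomes "can be obtained objectively and are taken from the medical records, and should therefore not be influenced by lack of masking". Three outcomes are taken out of that statement. One is named in the words "with the exceptions of global clinical improvement which is rated by clinicians"; the other two are the patient-rated quality of life and treatment satisfaction. Everything else stays inside it.

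Item d under Outcome measures lists the events at issue: "The number of attempted and completed suicides, incidences of physical violence, police arrests and days spent at work/training/education will also be recorded" over the 12 months. That item names no data source. The preceding item, on costs, does name one: service use "will be obtained from case notes and electronic administrative data bases". No police, employment or other outside source is described for item d.

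Researchers do not fill the gap. After recruitment, "there will be no requirement for further contacts between research assistants and patients in either group". The one optional later contact covers only the 11 patient-reported outcome questions.

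**The concern.** A record-based outcome is only as objective as the process that puts it in the record. The team gives the injection itself and logs it as given. A suicide attempt, a violent incident, an arrest or a day at college must first become known to a clinician, who then decides whether to note it. That clinician knows which arm the patient is in, so being in the notes does not protect these outcomes from the lack of masking.

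A second route runs beside the first. The incentive is meant to increase attended injections, each a meeting with a clinician. More meetings may mean more chances to hear of events.

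These outcomes carry weight. The article's section on risks and benefits expects lower suicide risk, fewer problems with the justice system and less harm to others. Its Discussion treats better health and social outcomes as what the intervention is finally for. Fuller capture under the incentive would hide a benefit on harm events or suggest a harm, and would inflate recorded work days. The bias therefore points in opposite directions for different outcomes.

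**Working it through.** The article gives no figure for how completely the notes capture these events, so there is none to reproduce. The check has a textual part and an illustration.

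**Textual part**

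- Exceptions to the claim (Design): clinician-rated improvement, quality of life, treatment satisfaction. The item d events are not excepted.
- Who writes the notes: team clinicians, unmasked (Design).
- Independent source for item d: none named. Administrative databases are named for service use and costs only (Outcome measures, item c).
- Research contact that could supplement the notes: none required (Design).

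So the claim covers item d, and nothing in the article supports it there.

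**Difference in injection contacts**

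Inputs: 65% of prescribed injections taken in control and 85% under the incentive, the planning means in Proposed sample size. The gap is 85 − 65 = 20 percentage points. Taking depot intervals of four, two and one weeks as examples (13, 26 and 52 injections a year), the extra injection contacts per patient-year are:

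- 4-weekly: 0.20 × 13 = 2.6
- 2-weekly: 0.20 × 26 = 5.2
- weekly: 0.20 × 52 = 10.4

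**Effect on recorded events**

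Assume equal true event rates in the two arms. Let f be the share of events that reach the notes without an injection contact. The documents do not give f, so it runs from 0 to 1. Assume the remaining events are captured in proportion to attendance:

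capture = f + (1 − f) × attendance

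spurious ratio = capture (incentive) / capture (control)

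For f = 0.50, control is 0.50 + 0.50 × 0.65 = 0.825 and incentive is 0.50 + 0.50 × 0.85 = 0.925, so the ratio is 0.925 / 0.825 = 1.12.

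| f | Control capture | Incentive capture | Spurious ratio |
|---|---|---|---|
| 0 | 65.0% | 85.0% | 1.31 |
| 0.25 | 73.8% | 88.8% | 1.20 |
| 0.50 | 82.5% | 92.5% | 1.12 |
| 0.75 | 91.3% | 96.3% | 1.05 |
| 0.90 | 96.5% | 98.5% | 1.02 |
| 1 | 100% | 100% | 1.00 |

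A ratio above 1 makes suicide attempts, violence and arrests look more frequent under the incentive, and work days more numerous. The table covers contact-dependent capture only. The documents offer no basis for putting a number on selective recording by unmasked staff.

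**The case against.** The case on the other side has several parts, and some of it stands.

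*The intervention need not raise contact much.* A reader might infer that every paid injection is an additional meeting. The documents do not support that: control patients are also prescribed depots and keep their usual care, so only the 20-point gap could be extra. Even that is an upper limit under the planning figures, because a patient may be visited and refuse the injection, and the teams do assertive outreach in both arms. This stands, and it is why the working uses only the gap.

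*Events reach the notes by other routes.* A reader might infer that notes capture events only during contact, and hence that ascertainment does differ by arm. Neither is stated. Arrests, violent incidents and suicide attempts can become known without an injection visit. This also stands: the difference is a possibility of unknown size. Ratios such as 0.90 / 0.50 = 1.80 need a wider capture gap than the planning figures produce under this model.

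*Silent notes need not count as zero.* The article states no such rule. Patients who cannot be traced and for whom outcome data cannot be had leave the analysis (Proposed sample size), and missing-data sensitivity analyses are planned. How silence is coded may be settled in documents not shown, so no error is alleged there.

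*The sentence is about masking, whereas contact-dependent capture would exist even in a masked trial.* The two mechanisms are indeed separate. But the sentence fails on masking alone, because unmasked staff decide what is written. Contact is a further reason not to treat these records as equally complete in both arms.

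*An article may leave extraction procedures to the full protocol.* True, and the absence of a form is not the finding. The finding is a stated property that does not follow for these outcomes.

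**Conclusion.** The claim of protection is wrong for the item d events. It is sound for injections taken, and can reasonably be kept for depot timing and admissions. The primary outcome is not affected.

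Differential ascertainment is a risk that the article dismisses without grounds; it is not an established fact. On the planning means of 65% and 85%, with no true effect, the spurious rate ratio lies between 1.00 and about 1.31. The upper end requires that no event reaches the notes except at an injection; if half or more arrive by other routes it is 1.12 or less. The range rests on equal true event rates, on capture proportional to attendance, and on the planned gap being the achieved one; a wider gap would raise the upper end. Since f is undocumented, no single value can be defended.

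The practical consequence is limited but real: a modest difference between arms in these events, in either direction, could not be read as an effect of the incentive without knowing how contact differed.

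**What to change.** 1. In the Design section, limit the claim of freedom from masking bias to injections taken, depot timing and admissions, and say explicitly that the item d events are excluded. This is a wording change.
2. Report the number of team contacts by arm, drawing largely on the outpatient and home-visit data already collected under item c, and interpret the item d comparisons in that light. The added cost is small.
3. Extract the item d events by the same procedure in both arms, keeping *none* distinct from *not known*.
4. Optionally, have staff complete one identical short form for every patient at 6 and 12 months. That is 136 × 2 = 272 forms and needs no patient contact, so it leaves the low-burden design intact. It may reduce the bias but does not remove it: it takes modest staff time and still relies on what unmasked staff know. It should not be presented as restoring the claim in step 1.

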### Planned interventions

Patients in the AOTs that have been allocated to the intervention will be offered a financial incentive for each depot injection of anti-psychotic medication for a 12 month period. Patients will receive £15 for one injection with the total sum not exceeding £60 for a four-week period (the maximum number of injections is 4 per month). The administering clinician will give the money in cash directly after the injection. Patients will sign a receipt. There are several reasons to set a standard sum of £15 for each depot injection:

• A fixed sum per injection simplifies the practice and makes it transparent for all clinicians and patients involved.

• The sum of £15 is in line with the successful open pilot study in East London.

• The sum is below the limit of £20 per week which would interfere with patients' disability benefits. Most patients eligible for the study receive Disability Living Allowance, Income Support with Disability Premium, or Incapacity Benefit. In all of these cases, patients are not entitled to have a separate income of more than £20 (including therapeutic earnings and income through research participation) without having their benefits reduced.

• £15 per injection is intended to be an incentive helping persuade otherwise ambivalent patients. Yet, it is important to limit the total sum to a maximum of £60 per four weeks so that patients do not become financially dependent on the additional income. The money is intended to provide an incentive, but not lead to financial dependence on the scheme.

Otherwise all patients will receive treatment as usual. The type, frequency and dosage medication and all other interventions will not be affected by participation in the study.

Members of the research team will attend meetings of each AOT in the intervention group and discuss again the practice of offering financial incentives and the nature of the study. Following that there will be a brief training programme on the exact procedure. The procedure of the intervention will also be outlined in a written manual. All teams will then be regularly visited by the research assistants and, if required, also by members of the team of applicants. A discussion of the practice at a team meeting will be repeated after 6 months of the intervention period.

